**Table 19: Summary of Primary Outcomes: Supportive Analyses, Not Pre-specified (Primary Ancillary Analysis Population)**

- repeat Table 18 in the Primary Ancillary Analysis population

| Table 20: Summary of Safety Events (Safety Population) |                        |                           |                                                                               |                                                                              |                                      |                      |                       |                  |      |
|--------------------------------------------------------|------------------------|---------------------------|-------------------------------------------------------------------------------|------------------------------------------------------------------------------|--------------------------------------|----------------------|-----------------------|------------------|------|
| Site                                                   | Number of Participants |                           |                                                                               |                                                                              |                                      |                      |                       | Number of Events |      |
|                                                        | Enrolled               | Received XR-BUP Injection | Experienced a 5 or greater increase in COWS score within 4 hours of injection | Transitioned to moderate withdrawal (COWS 13-24) within 4 hours of injection | Precipitated Withdrawal  | With at least One AE | With at least One SAE | AEs              | SAEs |
| Yale-New Haven Hospital ED                             | N                      | N                         | N (xx.x%)                                                                     | N (xx.x%)                                                                    | N (xx.x%)                            | N (xx.x%)            | N (xx.x%)             | N                | N    |
| Highland Hospital ED                                   |                        |                           |                                                                               |                                                                              |                                      |                      |                       |                  |      |
| Penn Presbyterian Medical Center ED                    |                        |                           |                                                                               |                                                                              |                                      |                      |                       |                  |      |
| Rhode Island Hospital ED                               |                        |                           |                                                                               |                                                                              |                                      |                      |                       |                  |      |
| San Leandro Hospital ED                                |                        |                           |                                                                               |                                                                              |                                      |                      |                       |                  |      |
| Total                                                  |                        |                           |                                                                               |                                                                              |                                      |                      |                       |                  |      |

 As captured on the Precipitated Withdrawal (PWD) CRF at the 240-minutes post injection visit.

Table 21: Summary of Safety Events (Safety Population, COWS 0-3)

- repeat Table 20 for safety population with baseline COWS 0-3

**Table 22: Summary of Treatment Emergent Adverse Events (Safety Population)**

|                                                                                               | Yale-New Haven Hospital ED (N=) | Highland Hospital ED (N=) | Penn Presbyterian Medical Center ED (N=) | Rhode Island Hospital ED (N=) | Total (N=) |
|-----------------------------------------------------------------------------------------------|---------------------------------|---------------------------|------------------------------------------|-------------------------------|------------|
| Number of participants with at least one treatment emergent adverse event (TEAE)  | N                               | N                         | N                                        | N                             | N          |
| Maximum severity of TEAE for participants with at least one TEAE  :               |                                 |                           |                                          |                               |            |
| Grade 1 - Mild                                                                                | N (x.x%)                        | N (x.x%)                  | N (x.x%)                                 | N (x.x%)                      | N (x.x%)   |
| Grade 2 - Moderate                                                                            |                                 |                           |                                          |                               |            |
| Grade 3 - Severe                                                                              |                                 |                           |                                          |                               |            |
| Number of participants with at least one TEAE related to study medication         | N (x.x%)                        | N (x.x%)                  | N (x.x%)                                 | N (x.x%)                      | N (x.x%)   |
| Number of participants diagnosed with COVID-19                                    | N (x.x%)                        | N (x.x%)                  | N (x.x%)                                 | N (x.x%)                      | N (x.x%)   |
| Number of TEAEs                                                                               | N                               | N                         | N                                        | N                             | N          |
| Severity of TEAEs                                                                 |                                 |                           |                                          |                               |            |
| Grade 1 - Mild                                                                                | N (x.x%)                        | N (x.x%)                  | N (x.x%)                                 | N (x.x%)                      | N (x.x%)   |
| Grade 2 - Moderate                                                                            |                                 |                           |                                          |                               |            |
| Grade 3 - Severe                                                                              |                                 |                           |                                          |                               |            |
| Relationship of TEAE to study medication                                          |                                 |                           |                                          |                               |            |
| No                                                                                            | N (x.x%)                        | N (x.x%)                  | N (x.x%)                                 | N (x.x%)                      | N (x.x%)   |
| Yes                                                                                           |                                 |                           |                                          |                               |            |

 The percentage is calculated with the denominator as the number of participants enrolled.

 The percentage is calculated with the denominator as the number of participants with TEAEs.

 The percentage is calculated with the denominator as the number of TEAEs.

**Table 23: Summary of Treatment Emergent Adverse Events (Safety Population, COWS 0-3)**

- repeat Table 22 for safety population with baseline COWS 0-3'

| Table 24: Summary of Treatment Emergent Adverse Events by MedDRA Coding (Safety Population) |                                 |                           |                                          |                               |            |
|---------------------------------------------------------------------------------------------|---------------------------------|---------------------------|------------------------------------------|-------------------------------|------------|
|                                                                                             | Yale-New Haven Hospital ED (N=) | Highland Hospital ED (N=) | Penn Presbyterian Medical Center ED (N=) | Rhode Island Hospital ED (N=) | Total (N=) |
| System Organ Class/Preferred Term (MedDRA V26.0)                                            |                                 |                           |                                          |                               |            |
| Participants with at least one treatment emergent adverse event (TEAE)                      | N                               | N                         | N                                        | N                             | N          |
| SOC1                                                                                        | N (x.x%)                        | N (x.x%)                  | N (x.x%)                                 | N (x.x%)                      | N (x.x%)   |
| PT                                                                                          | N (x.x%)                        | N (x.x%)                  | N (x.x%)                                 | N (x.x%)                      | N (x.x%)   |
| PT                                                                                          | N (x.x%)                        | N (x.x%)                  | N (x.x%)                                 | N (x.x%)                      | N (x.x%)   |
| ...                                                                                         |                                 |                           |                                          |                               |            |
| SOC2                                                                                        | N (x.x%)                        | N (x.x%)                  | N (x.x%)                                 | N (x.x%)                      | N (x.x%)   |
| ...                                                                                         |                                 |                           |                                          |                               |            |

Table 25: Summary of Treatment Emergent Adverse Events by MedDRA Coding (Safety Population, COWS 0-3)

- repeat Table 24 for safety population with baseline COWS 0-3'

**Table 26: Summary of Injection Site Assessments (Safety Population)**

|                                                                                                                                   | Yale-New
Haven
Hospital
ED
(N=) | Highland
Hospital
ED
(N=) | Penn
Presbyterian
Medical
Center ED
(N=) | Rhode
Island
Hospital
ED
(N=) | San
Leandro
Hospital
ED
(N=) | Total
(N=) |
|-----------------------------------------------------------------------------------------------------------------------------------|---------------------------------------------|------------------------------------|------------------------------------------------------|-------------------------------------------|------------------------------------------|---------------|
| Number of injection site assessments                                                                                | N (xx.x%)                                   |                                    |                                                      |                                           |                                          |               |
| Number of participants with delayed reaction since injection (reported after the initial injection site examination)  | N (xx.x%)                                   |                                    |                                                      |                                           |                                          |               |
| Number of participants experiencing at least one symptom                                                              | N (xx.x%)                                   |                                    |                                                      |                                           |                                          |               |
| Number of symptoms experienced                                                                                        | N                                           |                                    |                                                      |                                           |                                          |               |
| Pain                                                                                                                              | N (xx.x%)                                   |                                    |                                                      |                                           |                                          |               |
| Itching                                                                                                                           |                                             |                                    |                                                      |                                           |                                          |               |
| Discharge                                                                                                                         |                                             |                                    |                                                      |                                           |                                          |               |
| Tenderness                                                                                                                        |                                             |                                    |                                                      |                                           |                                          |               |
| Erythema/Redness                                                                                                                  |                                             |                                    |                                                      |                                           |                                          |               |
| Swelling                                                                                                                          |                                             |                                    |                                                      |                                           |                                          |               |
| Other                                                                                                                             |                                             |                                    |                                                      |                                           |                                          |               |
| Severity of pain                                                                                                      |                                             |                                    |                                                      |                                           |                                          |               |
| 0-3                                                                                                                               | N (xx.x%)                                   |                                    |                                                      |                                           |                                          |               |
| 4-7                                                                                                                               |                                             |                                    |                                                      |                                           |                                          |               |
| 8-10                                                                                                                              |                                             |                                    |                                                      |                                           |                                          |               |

 The Injection Site Assessment (ISR) form is expected at the Day 7 follow-up visit.

 The denominator for percentages is the number of participants enrolled.

 The denominator for percentages is the number of injection site assessments.

 The denominator for percentages is the number of symptoms experienced.

 The denominator for percentages is the number of pain symptoms experienced. Pain severity is reported on a scale from 0 to 10, with 10 being the most severe.

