| Mental Health Assessment (MHA)             |      | RA      |                   | X (if participant endorse suicidality on Heath Status Form; PHQ-9 question) |                  |                     |
| Adverse Events                             | X    |         |                   |                                                                             |                  |                     |
| Serious Adverse Events                     | X    |         |                   |                                                                             |                  |                     |
| Protocol Deviations                        | X    |         |                   |                                                                             |                  |                     |

*\*As a last resort, Day 7 assessments may be completed by phone except for UDS and COWS.*

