### 9.11.25 Injection Site Assessment Form

At 7-day follow up the participant will be queried about pain, itching, discharge and tenderness at the site. Study staff will examine the patient for erythema at the injection. Injection site reactions will not be reported on an Adverse Event form unless it meets criteria for an SAE.

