##### **3.1.1.4 Safety Population**

The safety population includes all participants who completed informed consent for the Ancillary component during the screening visit and received the XR-BUP injection. Pre-study participants are not included.

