### **8.1.4 Injection Site Assessments**

A summary table of injection site assessments will be provided by site. Injection site assessments are expected at the Day 7 follow-up visit. This will include the number and percent of injection site assessments, number and percent experiencing a delayed reaction since the injection, number and percent experiencing at least one symptom, the number of each symptom experienced and percent out of all symptoms experienced.

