### 8.2.2 Injection Site Assessments

A summary table of injection site assessments will be provided. Injection site assessments are expected at the Day 7 follow-up visit. This will include the number of injection site assessments, number and percent experiencing a delayed reaction since the injection, number and percent experiencing at each symptom, the number of each symptom experienced, and percent out of all symptoms experienced.

A listing of injection site reactions will be generated that includes the date of the assessment, the symptoms reported (and severity if applicable), and verbatim terms for any abnormalities categorized as 'other'.

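### SAP Table 26 prints each Day-7 injection-site reaction as a share of all symptoms, not of participants assessed, and Table 22's denominator wording conflicts with its Safety Population title

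*Combined protocol and SAP*

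**What the plan says.** **Injection-site table.** SAP 8.1.4 asks for "the number of each symptom experienced and percent out of all symptoms experienced". The shell for Table 26 (Safety Population) follows it, and footnote 4 on the named reactions reads "The denominator for percentages is the number of symptoms experienced". Two other rows of the same table, participants with a delayed reaction and participants with any symptom, use footnote 3: "The denominator for percentages is the number of injection site assessments". The row counting assessments done is divided by participants enrolled (footnote 2). Table 27 repeats Table 26 for baseline COWS 0-3.

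**Link to AE reporting.** Protocol 9.11.25 states: "Injection site reactions will not be reported on an Adverse Event form unless it meets criteria for an SAE".

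**Mode of the Day-7 visit.** Protocol 9.11.25 has staff inspect the site for erythema, and SAP Listing 6 marks redness and swelling as examination items. The footnote to protocol Table 3 allows this exception to in-person assessment: "As a last resort, Day 7 assessments may be completed by phone except for UDS and COWS".

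**AE table.** Table 22 is titled for the Safety Population, which SAP 3.1.1.4 limits to those who "completed informed consent for the Ancillary component during the screening visit and received the XR-BUP injection". Its footnote 1, on the participant-level rows, reads "The percentage is calculated with the denominator as the number of participants enrolled". Table 20, for the same population, counts enrolled and injected participants in separate columns.

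**The concern.** A reader of a safety table takes the percentage beside *pain* as the percentage of participants who had pain. In Table 26 it is not. Its denominator is the sum of the events being reported, so it moves only when the mix of reactions changes. It does not fall when reactions become rarer or rise when they become more common. The printed percentages for individual reactions therefore cannot be compared across sites, or between Table 26 and Table 27. The 25 additional participants were enrolled to learn more about COWS 0-3, so that second comparison matters.

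The AE tables cannot supply the missing figure, because non-serious injection-site reactions are kept off AE forms. No ancillary shell prints the Day-7 percentage of participants with each reaction.

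Table 22 raises a smaller question. Someone who never received the injection cannot have a treatment-emergent event. If the footnote is programmed literally, such people enter the denominator and lower the rate.

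**Working it through.** The shells are blank, so the plan has no figure to reproduce. All counts below are assumptions chosen to show how the rules behave.

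**1. Share of symptoms against risk (Table 26, footnote 4)**

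Let x be the number of participants with a given reaction, S the total number of symptoms and A the number of Day-7 assessments. The form is expected once per participant, so x counts people.

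- Printed by the plan: x / S
- Risk among those assessed: x / A

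Assume A = 80.

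| Case | Pain (x) | All symptoms (S) | Printed, x/S | Risk, x/A |
|---|---|---|---|---|
| Base: pain 20, tenderness 15, itching 10, redness 5 | 20 | 50 | 20/50 = 40.0% | 20/80 = 25.0% |
| Every count doubled | 40 | 100 | 40/100 = 40.0% | 40/80 = 50.0% |
| One painful injection, nothing else | 1 | 1 | 1/1 = 100% | 1/80 = 1.25% |

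Doubling the risk leaves the printed percentage unchanged. The two figures agree only when S = A.

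**2. What the table already gives**

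The any-symptom and delayed-reaction rows are divided by assessments. The number of assessments and the count of each reaction print in the same column. A reader can therefore compute x/A, but must set the printed percentage aside to do so.

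**3. Enrolled against injected (Table 22, footnote 1)**

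Let k be participants with a related event, E enrolled and I injected.

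- Literal reading of the footnote: k / E
- Safety Population reading: k / I
- Ratio of the first to the second: I / E, so the relative understatement is 1 − I/E, the share not injected

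With k = 20 and E = 100:

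| Injected | Footnote, k/E | Per injected, k/I | Relative understatement |
|---|---|---|---|
| 100 | 20.0% | 20.0% | 0% |
| 97 | 20.0% | 20.6% | 3% |
| 95 | 20.0% | 21.1% | 5% |
| 90 | 20.0% | 22.2% | 10% |

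The documents do not give the number enrolled but not injected. The disposition shell (Table 3) has a row for early terminations without study drug, so the plan allows for some.

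**4. Redness and swelling by phone**

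Listing 6 labels both as examination findings, and the Day-7 form may be completed by phone. If a phone assessment records them as absent rather than not examined, it adds to A without any chance of adding to x. The documents do not say how the form handles this, or how often phone was used, so no size can be given.

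**The case against.** The strongest reply is that little information is lost. Table 26 prints an overall local-reaction rate per assessment, and it prints the counts and the number assessed. Listing 6 shows each symptom per participant. A site with a single painful injection would show 1 (100%) under its own number of assessments, so the scale is visible. Local tolerability is also summarised elsewhere: pain scores after injection and at Day 7 (SAP 7.1.6.8, 7.1.7.8), and erythema and swelling at 30 and 240 minutes (SAP 7.1.6.9, 7.1.7.9). All of this stands, and it limits the point to the percentage printed for each individual reaction. It does not make that percentage informative.

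Four stronger readings are tempting, and the documents do not support them.

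- *The ancillary tables give no usable local-reaction rate, and COWS groups cannot be compared.* Footnote 3 and the printed counts show otherwise. Only the printed per-reaction percentages fail.
- *The RCT section already does this correctly.* SAP 8.2.2 lists "number and percent experiencing at each symptom", but the parallel item in 8.1.4 is the any-symptom count. The phrase is probably a garbled *at least one*, and 8.2.2 keeps the share-of-symptoms percentage too.
- *Table 22 is biased downward.* That holds only if the footnote is programmed literally and some participants were not injected. SAP 8.1 assigns ancillary safety analyses to the Safety Population, so *enrolled* may be loose wording. Table 30 footnote 4 uses the same term. Table 20's separate columns keep it ambiguous.
- *Phone visits dilute the reaction rate.* This assumes a recording practice that the documents do not describe, and phone is a last resort.

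**Conclusion.** The point holds for the individual reactions in Tables 26 and 27 and for the text of SAP 8.1.4. The prescribed percentage describes the composition of complaints and does not respond to the risk. The gap can be large (40.0% printed against 25.0% or 50.0% in the assumed example), but the right figure can be recovered from counts in the same table.

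Table 22 footnote 1 conflicts with the table's own population. The numerical effect is zero if everyone enrolled was injected and otherwise equals the share not injected, which is not stated. Table 26 footnote 2 describes form completion, not risk, and needs only the same wording alignment.

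These are descriptive safety tables for the ancillary component. No primary outcome and no criterion for expanding RCT eligibility depends on them. Severity is minor.

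**What to change.** 1. In SAP 8.1.4 and Tables 26 and 27, report each reaction as n (%) of participants with that reaction, over participants with a Day-7 injection-site assessment. Remove the share-of-symptoms percentage.
2. Where the form shows that redness or swelling was not examined, treat that item as missing, not absent, and leave the participant out of that item's denominator. First check that the form records this.
3. In Table 22 footnote 1, replace participants enrolled with the Safety Population N. Align the wording of Table 26 footnote 2 and Table 30 footnote 4.

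The cost is a few footnotes and one sentence of SAP text. Items 1 and 3 use data already planned for collection. Item 2 applies only as far as the form identifies items not examined. If the tables have already been run, only the affected percentages need re-running, and no design feature or test changes.
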